### 2.6. Intervention

The experimental (verum acupuncture) and placebo (sham acupuncture) groups will receive 9 acupuncture treatments. Both groups will be divided into two subgroups with a different treatment frequency: subgroup A will receive 3 acupuncture sessions per week over 3 weeks; and subgroup B will receive 1 acupuncture session per week over 9 weeks. The same selection of acupuncture points, identified according to the method of point location issued by the WHO [23], will be applied to both experimental subgroups A and B. Placebo subgroups A and B will receive acupuncture at the same non-specific acupuncture points. Details of the acupuncture intervention will be described according to the revised Standards for Reporting Interventions in Clinical Trials of Acupuncture (STRICTA) 2010 Checklist [24], as listed in Table 1.

## 3. Outcome Measurement

### 3.1. Primary Outcome

The primary outcome measure will be the change in the parameters of FC and HRQOL. FC will be measured by a 6-Minute Walk Test (6MWT) [28]. The 6MWT assesses the submaximal level of functional exercise capacity and is simple and convenient to carry out. Changes in the distance walked in 6 minutes will be used to evaluate the efficacy of therapeutic interventions.

Quality of Life will be assessed by Kidney Disease Quality of Life-Short Form (KDQOL-SFTM 1.3) [29]. The KDQOL-SF contains eight generic subscales that assess various aspects of HRQOL and has been widely used in CKD.

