## Abstract

The proposed randomized controlled trial protocol will evaluate the effect of acupuncture treatment on the functional capacity (FC) and health-related quality of life (HRQOL) in chronic kidney disease (CKD) with glomerular filtration rate (GFR) category 5 (CKG G5) patients receiving maintenance dialysis. Patients undergoing hemodialysis (HD) from a dialysis center will be randomly assigned to experimental, placebo and control groups. In order to determine the difference between the same number of treatments performed three times or one treatment a week, experimental (verum acupuncture) and placebo (sham acupuncture) groups will receive a total of nine acupuncture treatments; however, both groups will be divided into subgroups A and B. The same selection of acupuncture points will be applied to both experimental subgroups and the placebo subgroups will receive acupuncture on non-acupuncture points. The results will be assessed by the 6-min Walk Test, Handgrip Test, 30-sec Sit-to-Stand and Kidney Disease Quality of Life-Short Form and will be held at baseline, after treatment and 12 weeks post-treatment follow up. This paper describes the rationale and design for a randomized, patient-assessor blinded controlled trial, which may provide evidence for the clinical application of acupuncture in CKG G5 patients undergoing HD.

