### 3.4. Statistical Analysis and Sample size

Demographic and clinical data for each group at baseline will be compared using Fishers’ Exact Test (categorical variables) and one-way ANOVA (continuous variables). Two-way repeated-measures ANOVA with interaction between time (baseline, 3 weeks, 9 weeks and follow-up period 12 weeks after treatment) and group will be used to assess the effect of the treatment. Differences over time within each group and subgroup will be assessed with repeated-measures ANOVA, and differences among groups at each moment will be evaluated with one-way ANOVA. A significance level of 5% will be used; differences will be considered statistically significant for *p*-value < 0.05. Statistical analysis will be performed with IBM SPSS Statistics software, version 27.0, IBM, New York, NY, USA [33].

For the sample size, a minimum of 20 patients in each group (experimental, placebo and control groups) was estimated to achieve a small to medium effect size (f = 0.19) [34] in the two-way repeated-measures ANOVA, with a statistical power of 80% and a significance level of 5%. Sample-size calculations were carried out using G*Power V.3.1 [35]. Assuming a possible dropout rate of 15%, a minimum of 24 patients will be randomly selected for each group. In the experimental and placebo groups, half of the patients (*n* = 12) will be placed in subgroup A, with three acupuncture sessions per week over 3 weeks, and half (*n* = 12) will be placed in subgroup B, with one acupuncture session per week over 9 weeks.

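### Two primary domains, one of them an eight-subscale questionnaire, have no lead score and no success rule, while every test is judged at 5% and the trial is sized for one test

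*Protocol article*

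**What the plan says.** Section 3.1 of the protocol article defines the primary outcome as follows: "The primary outcome measure will be the change in the parameters of FC and HRQOL". The first domain is measured by 6MWT distance. The second is measured by the KDQOL-SF, about which the section says: "The KDQOL-SF contains eight generic subscales that assess various aspects of HRQOL". It names no summary score, lead subscale or primary time point, and no rule for combining the two domains.

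Section 3.4 assigns the treatment effect to a "Two-way repeated-measures ANOVA with interaction between time (baseline, 3 weeks, 9 weeks and follow-up period 12 weeks after treatment) and group". It adds repeated-measures ANOVA within each group and subgroup, and says that "differences among groups at each moment will be evaluated with one-way ANOVA". One rule covers all of these: "A significance level of 5% will be used". No adjustment or order of testing is stated.

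The sample size in the same section is for one two-way repeated-measures ANOVA with f = 0.19, 80% power and a 5% level. It gives 20 patients per group, or 24 after 15% dropout. The section does not say which outcome f = 0.19 refers to.

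**The concern.** The sample size presumes one primary test at 5%, but the outcome section does not define one. Between two and nine scores can be read as primary, each compared with 0.05, and the article does not say which of them must succeed. If one significant score is enough, the chance of a false primary claim exceeds the stated 5%. The score that carries the claim could also be chosen after the data are seen. That would weaken the trial's second objective (section 1), the comparison of acupuncture with placebo.

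**Working it through.** **1. The plan's own sample size.** Inputs from section 3.4 are f = 0.19, level 0.05, power 80% and k = 3 groups. The correlation between repeated measures (ρ = 0.5) and the sphericity parameter (ε = 1) are assumed, because the article gives neither. For the group-by-time interaction:

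- λ = f²·N·m/(1 − ρ), df1 = (k − 1)(m − 1), df2 = (N − k)(m − 1).
- The abstract says assessments "will be held at baseline, after treatment and 12 weeks post-treatment follow up", so m = 3. At N = 60, λ = 0.0361 × 60 × 3/0.5 = 13.0 with 4 and 114 degrees of freedom, and power is 0.819. The smallest N for 80% is 58, which rounds up to 60, or 20 per group.
- Dropout: 20/0.85 = 23.5, so 24 per group.

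The stated figures reproduce, as the size of one interaction test at 5%. With the four times listed in section 3.4, N would be 50 (17 per group), which does not match.

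**2. Number of primary scores.** 6MWT contributes one. The KDQOL-SF contributes one if a single score is meant, or eight if each subscale is. The count is therefore two or nine.

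**3. False-positive rate if any one score suffices.** Under independence it is 1 − 0.95^K:

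- K = 2: 1 − 0.95² = 0.0975
- K = 9: 1 − 0.95⁹ = 0.370

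Scores from the same patients are correlated, and the article gives no correlations, so a range was simulated under equal pairwise correlation. One set used two-sided z tests. The other used group-by-time F tests with 20 per group, for m = 3 and m = 4.

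| Assumed correlation | Nine scores, z tests | Nine scores, F tests | Two scores, z tests |
|---|---|---|---|
| 0.3 | 0.33 | 0.33–0.34 | 0.095 |
| 0.5 | 0.27 | about 0.285 | 0.091 |
| 0.7 | 0.20 | 0.21–0.22 | 0.084 |
| 0.8 | 0.17 | 0.18 | 0.078 |
| 0.9 | 0.12 | 0.13 | 0.070 |

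**4. If both domains must succeed.** With quality of life as one score, the rate does not exceed 5%. If any of the eight subscales could satisfy the quality-of-life requirement, that part alone would have an error of up to 1 − 0.95⁸ = 0.337 under independence.

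**5. Power under alternative remedies** (m = 3, ρ = 0.5, ε = 1):

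| Approach | Level per test | Power at N = 60 | Per group for 80% | After 15% dropout |
|---|---|---|---|---|
| First test in a fixed order | 0.05 | 0.82 | 20 | 24 |
| Bonferroni, two scores | 0.025 | 0.73 | 23 | 28 |
| Bonferroni, nine scores | 0.0056 | 0.53 | 30 | 36 |

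**The case against.** The strongest reply is that the article does not say what the larger figures require. Its remark about eight subscales describes the questionnaire; it does not declare eight primary tests. No sentence says that one significant score makes the trial positive. The Discussion (section 4) expects gains in walking distance and quality of life together. A multiplicity rule and the choice of KDQOL-SF score may also sit in an analysis plan that is not shown, and adjusted p-values would be compared with 0.05 too.

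Much of this stands. A reader might infer that the trial has a false-positive rate of 21–37%. The documents do not support that as a fact, because it needs all eight subscales to be primary, any one to suffice, and a correlation no higher than about 0.7. A reader might also multiply the nine scores by the number of visits and reach a much larger figure. That would treat repeated measurements on the same patients as independent. It would also count per-visit ANOVAs that section 3.4 lists apart from the treatment-effect test and nowhere makes a route to the primary claim.

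The reply does not remove the defect. The Discussion sentence is an expectation, not a decision rule, and it speaks of quality-of-life scores in the plural. The choice of primary outcome belongs in the protocol, and section 3.1 makes that choice without settling it. The 5% rule and the single-test sample size are likewise fixed in this article.

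**Conclusion.** The point holds in conditional form. The article names two primary domains without a lead score or success rule, applies p < 0.05 throughout with no adjustment stated, and sizes the trial for one test. Its size depends on a reading that the article leaves open:

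- either domain suffices, quality of life as one score: up to 9.8%;
- any of nine scores suffices: up to 37% under independence, about 21% at correlation 0.7, and about 12–18% at 0.8–0.9;
- both domains required, quality of life as one score: no more than 5%.

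The correlations are assumptions, and the figures count one test per score. The article does not say which reading applies, so the stated 5% cannot be relied on for the primary claim. This should be corrected; it does not call for a redesign.

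**What to change.** In sections 3.1 and 3.4:

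1. Keep the group-by-time repeated-measures test on which the sample size rests, and state which measurement times enter it.
2. Apply it in a fixed order at 5%: first to 6MWT distance, then to one KDQOL-SF score named in advance. Holm across these two scores is an alternative if neither domain should come first.
3. Label the remaining KDQOL-SF subscales, the per-visit ANOVAs and the within-group and within-subgroup ANOVAs as supportive, and report them with confidence intervals.
4. If a verum-versus-sham contrast is to be the primary test instead, define the end of treatment, which falls at week 3 in subgroup A and week 9 in subgroup B (section 2.6), and restate the power for that contrast. As a guide, a plain two-sample t-test with 20 per arm needs a standardised difference of about 0.91 for 80% power.

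The first three items change wording only, and under the fixed order 20 per group (24 with dropout) stands. The downside is that quality of life can be claimed only if the 6MWT test is positive, although the first objective in section 1 lists the two domains side by side. Holm avoids that ranking at some loss of power: if both scores share the same f = 0.19, each has power between 0.73 and 0.82 at N = 60.

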### 3.2. Secondary Outcomes

Secondary outcome measures will be changes in handgrip and lower-limb strength. Handgrip strength will be measured by a Hand Grip Strength (HGS) test [30,31], using a digital dynamometer. The HGS test is an indicator of overall muscle strength and is commonly used.

Lower-limb strength will be measured by a 30 s Sit-to-Stand (30STS) test [32]. Demographic, clinical variables and blood analytical data will be collected using a Sociodemographic and Clinical Data Collection Form in the baseline period. Pre- and post-intervention questionnaires will be applied before and after the treatment period. The outcome measurement time points are detailed in Figure 2.

### 3.3. Participant Timeline

The timeline for the study visits, enrolment process, interventions, assessments, and follow-ups carried out on the participants will be reported based on the Standard Protocol Items: Recommendations for Interventional Trials (SPIRIT) guidelines [20], as shown in Figure 2.

### 3.4. Statistical Analysis and Sample size

Demographic and clinical data for each group at baseline will be compared using Fishers’ Exact Test (categorical variables) and one-way ANOVA (continuous variables). Two-way repeated-measures ANOVA with interaction between time (baseline, 3 weeks, 9 weeks and follow-up period 12 weeks after treatment) and group will be used to assess the effect of the treatment. Differences over time within each group and subgroup will be assessed with repeated-measures ANOVA, and differences among groups at each moment will be evaluated with one-way ANOVA. A significance level of 5% will be used; differences will be considered statistically significant for *p*-value < 0.05. Statistical analysis will be performed with IBM SPSS Statistics software, version 27.0, IBM, New York, NY, USA [33].

For the sample size, a minimum of 20 patients in each group (experimental, placebo and control groups) was estimated to achieve a small to medium effect size (f = 0.19) [34] in the two-way repeated-measures ANOVA, with a statistical power of 80% and a significance level of 5%. Sample-size calculations were carried out using G*Power V.3.1 [35]. Assuming a possible dropout rate of 15%, a minimum of 24 patients will be randomly selected for each group. In the experimental and placebo groups, half of the patients (*n* = 12) will be placed in subgroup A, with three acupuncture sessions per week over 3 weeks, and half (*n* = 12) will be placed in subgroup B, with one acupuncture session per week over 9 weeks.

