### 3.6. Quality Control and Data Collection

Before the clinical trial begins, the research team will receive specialized training to ensure the quality of the study is maintained. Topics concerning the research process, eligibility criteria, data collection and management and assessment of adverse events will be covered.

Screening for eligibility, demographic and clinical-data collection and physical examinations will be performed by the TECSAM clinical team, acting as an independent assessor. The main researcher, the practitioner who will provide the acupuncture treatments, will not have access to patient data until anonymization, randomization and allocation procedures are complete. Baseline, after-treatment and follow-up outcome variables will be assessed by the TECSAM head nurse, who will not know to which group each subject is assigned. Moreover, the statistician will be unaware of the allocation details during the research period, to ensure that the objectivity and impartiality of the data are guaranteed.

The clinical trial will be stopped in case of serious adverse events. Participants will be withdrawn from the study if they are reluctant to continue or if they ask to be excluded.

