Many pharmacological interventions for people with CKD have known risks of adverse events and, according to the literature, acupuncture is commonly used in symptom management for chronic diseases as well as in palliative care [42]. However, the safety and efficacy of acupuncture for people with CKD remains largely unknown. Considering the aims of our study, we expect that verum acupuncture compared to sham acupuncture and non-acupuncture will improve the functional capacity of hemodialysis patients, as evidenced by an increase in the distance walked on the 6MWT and an increase in scores for quality of life. In addition, we expect an increase in handgrip strength and an improvement in peripheral muscle strength. According to Kim et al. (2016), there was low-quality evidence of the short-term effects of manual acupressure as an adjuvant intervention for fatigue, depression, sleep disturbance and uremic pruritus in patients undergoing regular hemodialysis [19]. Under this assumption, this study protocol was designed to check the effect of acupuncture after treatment and at 12 weeks post-treatment. In this way, we expect that the effect of acupuncture will be maintained in the follow-up period.

Some studies, especially in the pain field, suggest that three treatments per week obtain better results than one treatment per week [43,44]. We also expect to see better results with more intensive interventions compared to less frequent and prolonged interventions.

Following review of the literature and to the best of the authors’ knowledge, there are currently no comparable studies. Therefore, our trial seems to be an innovative study for exploring the effect of acupuncture and the frequency of treatment on improving FC and HRQOL in patients undergoing HD. Furthermore, supported by only a few clinical cases reported (personal data) prior to the design and development of the research project, it is possible to predict efficacy and the advantages of integrating acupuncture treatments into routine hemodialysis as a complementary therapy to conventional treatments.

Despite fulfilling strict methodological criteria, it is possible to identify limitations in our study protocol. First, the sample size; second, the TCM practitioner performing the acupuncture treatment will not be blinded due to the nature of the intervention; third, comorbidities inherent to chronic kidney disease may lead to a high dropout rate during the follow-up period.

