	(6b) Precise description of the control or comparator. If sham acupuncture or any other type of acupuncture-like control is used, provide details as for Items 1 to 3 above.	The placebo group (sham acupuncture) will receive a total of 9 acupuncture treatments, however, will be divided into subgroups A and B. Placebo subgroup A will receive three acupuncture sessions per week over 3 weeks and subgroup B will receive one a week for 9 weeks. Manual acupuncture will be performed as superficial needling (5 mm depth) at non-acupuncture points without an attempt to achieve a *De qi* sensation and without stimulation, lasting 25 min, using a sterilized stainless-steel needle (0.25 × 25 mm; Tewa, asia-med GmbH, [name]).The control group (waiting list) will not receive any acupuncture treatment during the study period. **List of Non-Acupuncture points used and their location** In the present study, the non-acupuncture points selected will be the points located on the non-meridian but near the acupuncture points described above. Non-Acupuncture point 1 (NA1) Located near KI3 (*Taixi*). On the posteromedial aspect of the ankle, at the midpoint of KI3 (*Taixi*) and (*Fuliu*). KI7 (*Fuliu*) is located on the posteromedial aspect of the leg, anterior to the calcaneal tendon, 2 *cun* superior to the prominence of the medial malleolus. Non-Acupuncture point 2 (NA2) Located near SP6 (*Sanyinjiao*). On the leg, at the midpoint of the medial side of the tibia, 1 *cun* distal from SP6 (*Sanyinjiao*). Non-Acupuncture point 3 (NA3) Located near ST36 (*Zusanli*). On the anterior aspect of the leg, at midpoint of ST37 (*Shangjuxu*) and the Gallbladder Meridian. ST37 (*Shangjuxu*) is located on the anterior aspect of the leg, on the line connecting ST35 with ST41, 6 *cun* inferior to ST35, on the tibialis anterior muscle. Non-Acupuncture point 4 (NA4) Located near HT7 (*Shenmen*). On the wrist, at the transverse crease of the wrist, at the midpoint of HT7 (*Shenmen*) and PC7 (Daling), between the Pericardium Meridian and the Heart Meridian. Non-Acupuncture point 5 (NA5) Located near CV4 (*Guanyuan*). On the lower abdomen, 1 *cun* lateral from CV6 (*Qihai*). CV6 (*Qihai*) is located 1.5 *cun* inferior to the center of the umbilicus, on the anterior median line.

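### The four calendar time levels of the main ANOVA do not match the treatment-anchored assessments or the two schedules pooled within each acupuncture group

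*Protocol article*

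**What the plan says.** Section 3.4 sets out the main efficacy analysis as a "Two-way repeated-measures ANOVA with interaction between time (baseline, 3 weeks, 9 weeks and follow-up period 12 weeks after treatment) and group". It sizes the trial on three groups (verum, sham, control) and mentions subgroups separately, so group in this test means those three arms.

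Other sections describe the assessments differently:

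- Abstract: outcome measurements "will be held at baseline, after treatment and 12 weeks post-treatment follow up".
- Section 3.6: "Baseline, after-treatment and follow-up outcome variables will be assessed by the TECSAM head nurse".
- Discussion: the trial was "designed to check the effect of acupuncture after treatment and at 12 weeks post-treatment".

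On schedules, section 2.6 states that "subgroup A will receive 3 acupuncture sessions per week over 3 weeks" and that "subgroup B will receive 1 acupuncture session per week over 9 weeks". Under section 3.4, each acupuncture group holds 12 patients on each schedule. Table 1 (item 6b) adds: "The control group (waiting list) will not receive any acupuncture treatment during the study period". Sections 3.2 and 3.3 refer to Figure 2 for visit timing, and that figure is not reproduced in the text available here.

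**The concern.** Three sections anchor the outcome to each patient's own treatment: before it, at its end, and 12 weeks later. Section 3.4 uses two calendar weeks in the middle and a treatment-anchored follow-up at the end. Week 3 and week 9 are each the end of treatment for only half of each acupuncture group.

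At stake is what the main group-by-time test estimates. The Introduction asks for short- and long-term effects against placebo. A level that averages finished and unfinished patients, or just-finished patients and patients six weeks off treatment, is neither the effect after treatment nor a clean measure of maintenance. The one-way ANOVAs planned at each moment inherit the same levels.

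**Working it through.** **1. Count the assessments.** Abstract, section 3.6 and Discussion: baseline, after treatment, follow-up, so three. Section 3.4: four levels. Nothing in the text reconciles them.

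**2. Place the schedules on the calendar** (section 2.6; weeks from the start of treatment).

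| Level in section 3.4 | Subgroup A | Subgroup B |
|---|---|---|
| 3 weeks | 9 of 9 sessions, just finished | about 3 of 9 sessions |
| 9 weeks | 9 − 3 = 6 weeks off treatment | 9 of 9 sessions, just finished |
| 12 weeks after treatment | 3 + 12 = week 15 | 9 + 12 = week 21 |

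**3. Reading 1: every patient is measured at weeks 3 and 9.** Mean sessions received at week 3 in a pooled acupuncture group: (12 × 9 + 12 × 3)/24 = 6 of 9. Week 9 pools end of treatment with six weeks off treatment.

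**4. Reading 2: each patient is measured only at the end of their own treatment.** A has no week-9 value and B no week-3 value. Patients with all four values: 0 of 24 in verum and 0 of 24 in sham. A complete-case repeated-measures ANOVA of the stated factor cannot be fitted to them. Controls could still have all four.

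**5. Reading 3: 3 weeks (A) and 9 weeks (B) are meant as one after-treatment level.** This fits the three-assessment text, but the factor would then have three levels, not the four that section 3.4 lists.

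**6. Size under reading 1, as an illustration.** None of these inputs is in the protocol: 20 per arm, half on each schedule; correlation 0.5 between visits; verum effect 0.855 SD over sham at end of treatment; B's effect proportional to sessions received; at week 9, A keeps either all or half of its effect. With correlation 0.5, the SD of change from baseline is √(2 × (1 − 0.5)) = 1 SD. The two-sample noncentrality is d/√(2/20), with 38 degrees of freedom.

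- Own end of treatment: d = 0.855, noncentrality 2.70, power 75%.
- Week 3: d = (0.855 + 0.285)/2 = 0.570, noncentrality 1.80, power 42%.
- Week 9, half of A's effect lost: d = (0.4275 + 0.855)/2 = 0.641, noncentrality 2.03, power 51%.
- Week 9, no loss: d = 0.855, power 75%.

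This closed form ignores the extra spread from A and B having different means within the verum arm. Simulation that includes it gives about 40% at week 3 and about 49% at week 9 with half lost; the 75% figures do not change.

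**7. The stated sample size.** Within-between interaction in G*Power: λ = f²·N·m·ε/(1 − ρ), df1 = (k − 1)(m − 1)ε, df2 = (N − k)(m − 1)ε, with k = 3 groups, f = 0.19 and α = 0.05. Section 3.4 gives neither ρ nor ε.

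| Levels m | ρ | ε | Per group for 80% | Power at N = 60 |
|---|---|---|---|---|
| 3 | 0.5 | 1 | 20 | 0.819 |
| 4 | 0.5 | 1 | 17 | 0.885 |
| 4 | 0.4 | 1 | 20 | 0.810 |
| 4 | 0.5 | 0.80 | 20 | 0.823 |
| 4 | 0.5 | 0.75 | 20 | 0.803 |

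For the first row, λ = 0.0361 × 60 × 3/0.5 = 13.0 on 4 and 114 degrees of freedom. Dropout: 20/0.85 = 23.5, rounded up to 24, as stated. The figure of 20 is therefore reproduced, but it does not identify the number of levels.

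**The case against.** The strongest reply is that Figure 2 defines the visits and cannot be seen here, so the schedule should not be called faulty. This stands in part. The figure may say when controls are assessed, so a reader who infers that control timing is undefined goes further than the documents allow. But the figure could only show which reading applies. Visits for all at both weeks leave the mixing in place; visits only at each patient's own treatment end leave the stated factor unfittable in the acupuncture groups.

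A second reply is that the authors simply meant reading 3. That is plausible, and under it neither failure occurs. Section 3.4 does not say so, however, and the listed levels would need correcting.

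A third is that section 3.4 also plans repeated-measures ANOVA within each subgroup, so each schedule's course will be seen. True, but those tests compare a subgroup with itself over time. They do not repair the comparison with sham or control.

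A fourth is that the power losses depend on assumptions. This stands. The Discussion expects the effect to be maintained at follow-up, and with no loss the week-9 comparison is as powerful as the aligned one. The week-3 loss rests on an effect that grows with sessions received.

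A reader might also infer that 20 per group could only have come from three levels, and so contradicts the four-level analysis. The calculation does not support that: four levels give 20 under several ordinary choices of ρ and ε.

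**Conclusion.** The point holds. As written, the time factor conflicts with the three treatment-anchored assessments described elsewhere. It either mixes on-treatment, end-of-treatment and off-treatment values in the pooled groups, or leaves no verum or sham patient with a complete row. If a single after-treatment level was intended, the factor is misstated. In each case section 3.4 needs correction. This is more than detail left to an analysis plan, because the article fixes the levels.

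The contradiction and the session counts follow from the text alone. The size is illustrative: under the assumed effect, correlation and proportionality to sessions, power is about 40% at week 3, about 49% (half of A's effect lost) to 75% (none lost) at week 9, and about 75% at each patient's own end of treatment. It is not established that the sample size is wrong, that control visits are unplanned, or that the main test must lose power whatever the decay.

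**What to change.** - Reconcile the Abstract and sections 3.4 and 3.6, in agreement with Figure 2.
- Base the main group-by-time test on three levels aligned to treatment: baseline, end of own treatment (week 3 for A, week 9 for B), and 12 weeks after it (week 15 for A, week 21 for B). Include schedule (A/B) as a factor.
- Compare with control values at the matching calendar weeks. If controls are seen at both week 3 and week 9, use both; otherwise assign each control to a matching calendar. Treat the follow-up weeks the same way.
- If all patients are measured at both weeks, keep those data and report week-3 and week-9 means by schedule.
- State the number of time levels, the correlation and ε used for the sample size.

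The cost is revised wording, a little more analysis work and possibly a visit calendar for controls. Whether any visit has to be added depends on Figure 2.

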The fundamental questions guiding our entire research project are: What is the effect of TCM therapeutic strategies in the improvement of symptoms resulting from renal replacement therapy in CKG G5 patients undergoing HD? Does acupuncture have a positive effect on FC and health-related quality of life (HRQOL) in hemodialysis patients? If it does, are the results maintained over the long term? In addition, what is the effectiveness of short-term intensive interventions when compared to less frequent and prolonged interventions? Is it possible to integrate acupuncture into the dialysis care routine? Given our research project and the complexity of CKD, the objectives of this study are: (1) to assess the effect of acupuncture on FC and HRQOL in patients undergoing hemodialysis; (2) to evaluate the specific effects of acupuncture as compared to a placebo; (3) to evaluate short- and long-term effects of acupuncture; (4) to determine the difference between short-term intensive and ongoing but less frequent acupuncture treatments; (5) to assess the feasibility of integrating acupuncture in dialysis care.

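### No stated analysis compares the two treatment frequencies: subgroups A and B get only separate tests of change over time, so objective 4 is left untested

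*Protocol article*

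**What the plan says.** The frequency question is a between-schedule question wherever the protocol article raises it. Objective 4 in the Introduction is "to determine the difference between short-term intensive and ongoing but less frequent acupuncture treatments". The Abstract gives it as the reason for having subgroups: "In order to determine the difference between the same number of treatments performed three times or one treatment a week". The Discussion adds an expected direction: "We also expect to see better results with more intensive interventions compared to less frequent and prolonged interventions".

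Section 3.4 lists the analyses. The main model is a two-way repeated-measures ANOVA that crosses the four assessment times with the three groups, and its stated purpose is to judge the treatment effect. For subgroups it says "Differences over time within each group and subgroup will be assessed with repeated-measures ANOVA". The cross-sectional comparison is that "differences among groups at each moment will be evaluated with one-way ANOVA". The sample-size paragraph of the same section shows what is meant by group: "a minimum of 20 patients in each group (experimental, placebo and control groups"). The verum and sham groups each hold 12 patients in A and 12 in B. Section 2.4 forms these subgroups by order: the first 12 randomised in each group go to A and the remaining 12 to B.

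**The concern.** A repeated-measures ANOVA inside subgroup A asks whether A changed. The same test inside B asks whether B changed. Neither asks whether A and B differ, and two separate answers do not add up to a test of the difference. Section 3.4 does not leave the subgroup analysis open. It names one, and that one cannot answer objective 4.

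With nothing else in the plan that bears on frequency, the only material for a conclusion would be a pair of within-subgroup p-values from about 12 patients each. At that size, one being below 0.05 and the other above it is a common chance result even when the schedules are equivalent. A non-significant change in one small subgroup could then pass for inferiority of that schedule. The sham subgroups could help to show how much of an A-B difference comes from contact frequency alone, but no stated analysis uses them for that.

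**Working it through.** **Inputs.** From section 3.4: f = 0.19, alpha 5%, power 80%, 20 per group, 15% dropout, 24 per group randomised, 12 per subgroup, four time points. About 10 per subgroup remain after dropout (12 × 0.85 = 10.2). Assumed, because the article gives neither: correlation between repeated measures ρ = 0.5, and sphericity (ε = 1).

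**1. The plan's own figure.** For the time-by-group interaction, λ = f²·N·m/(1 − ρ), with df (k − 1)(m − 1) and (N − k)(m − 1).
- k = 3, m = 3, N = 60: λ = 0.0361 × 60 × 3 / 0.5 = 13.0, df 4 and 114, power 0.819. The smallest balanced N is 60, so 20 per group is reproduced. Dropout: 20 / 0.85 = 23.5, rounded up to 24.
- With the four time points listed in section 3.4, power at N = 60 is 0.885 and 17 per group would do.

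The calculation is for the three groups and does not address A against B.

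**2. Which stated test addresses objective 4?**

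| Analysis in section 3.4 | Units compared | Tests A vs B? |
|---|---|---|
| Two-way RM-ANOVA, time × group | three groups | no |
| RM-ANOVA over time | one group or subgroup at a time | no |
| One-way ANOVA at each moment | groups | no |

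**3. What a pair of within-subgroup tests would show if A and B respond identically.** For one subgroup, λ = f²·n·m/(1 − ρ), df (m − 1) and (n − 1)(m − 1), giving power q. The chance that exactly one of two independent tests is significant is 2q(1 − q), which cannot exceed 50%.

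At n = 12, m = 4, f = 0.19: λ = 0.0361 × 12 × 4 / 0.5 = 3.47, df 3 and 33, q = 0.282, and 2 × 0.282 × 0.718 = 0.405. A simulation of 20,000 trials gave 0.407.

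| True f in both subgroups | n = 12 | n = 10 |
|---|---|---|
| 0 | 10% | 10% |
| 0.10 | 19% | 17% |
| 0.19 | 40% | 36% |
| 0.25 | 50% | 47% |
| 0.30 | 46% | 50% |
| 0.40 | 20% | 31% |

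Sensitivity to ρ at f = 0.19, n = 12: ρ = 0.3 gives λ = 2.48, q = 0.209, 33%; ρ = 0.7 gives λ = 5.78, q = 0.451, 50%. In the same simulations, a direct time-by-subgroup interaction test rejected in about 5% of runs at every f.

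**4. What a direct comparison could detect.** These are single-time-point contrasts, two-sided 5%, 80% power, in units of the outcome SD. A vs B within verum has noncentrality d√(n/2) on 2n − 2 df. The schedule-by-needling interaction, (A − B in verum) − (A − B in sham), has twice the variance, so noncentrality d√(n/4) on 4n − 4 df. Baseline adjustment multiplies the result by about √(1 − 0.5²) = 0.866.

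| Contrast | 12 per cell | 10 per cell | 12, adjusted | 10, adjusted |
|---|---|---|---|---|
| A vs B in verum | 1.197 | 1.325 | 1.036 | 1.147 |
| Schedule × needling | 1.654 | 1.821 | 1.432 | 1.577 |

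As a time-by-subgroup interaction within verum at f = 0.19, power is 0.49 (three time points) to 0.56 (four) with 12 vs 12, and 0.41 to 0.47 with 10 vs 10.

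**5. Timing.** Nine sessions end at week 3 in A (9/3) and week 9 in B (9/1). At week 3, B has had about three sessions. The follow-up 12 weeks after treatment falls at week 15 in A and week 21 in B.

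**The case against.** The strongest reply is that this is an argument from silence in a condensed article. The contrast for the fourth of five objectives may be set out in a full protocol or analysis plan that is not shown, and within-subgroup tests of change are a legitimate description in their own right. This does not clear the point, because section 3.4 states its set of analyses and gives subgroups one that does not match the objective. It does mean one cannot say that no A-vs-B comparison will ever be made.

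A second reply is that the one-way ANOVA among groups might be meant to cover subgroups. The sentence itself separates group and subgroup from groups, so this is not its natural reading. Even if it were, the test would be cross-sectional at each visit, and at week 3 it would mix schedule with number of sessions received.

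A reader might infer that the investigators will treat one significant and one non-significant subgroup as a frequency difference. Nothing in the article says so, and the error rates in step 3 apply only if that is done. Nor is there one error rate: it depends on the unknown effect and correlation, and a figure near 50% is the maximum of the range.

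Two further complaints would go too far. Stating an expected direction is only a hypothesis, and a separate power statement for this objective is not obligatory; the Discussion already lists sample size first among the limitations.

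**Conclusion.** The point stands as a mismatch between objective and analysis: as written, section 3.4 contains no test of three sessions a week against one. This follows from the text and needs no assumption.

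The size of the risk is conditional. If the two within-subgroup results were used to judge frequency, equivalent schedules would give a discordant pair in about 10% to 50% of trials, and in about 40% at f = 0.19 with 12 per subgroup, four time points, ρ = 0.5 and sphericity.

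A reader might also infer that adding the missing contrast would turn objective 4 into a sound randomised comparison. The article does not support that. Section 2.4 assigns schedule by order of randomisation, so A vs B is confounded with enrolment period to the extent that entry is spread over time, and the two schedules reach end of treatment six weeks apart (9 − 3). The sham contrast, formed the same way, offsets this only in part. With 10 to 12 per cell, only large differences are detectable. The objective can be explored but not settled here.

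**What to change.** In section 3.4, or in the analysis plan if one exists:

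- Specify for objective 4 the baseline-adjusted A-minus-B difference within verum, and its difference from A-minus-B within sham, at end of treatment and at 12 weeks after treatment, each with a 95% CI.
- State that no conclusion about frequency will rest on within-subgroup p-values. Means and intervals by subgroup can stay as description.
- Label objective 4 exploratory and give the 80%-power detectable differences: about 1.0 to 1.3 SD for A vs B within verum, and about 1.4 to 1.8 SD for the schedule-by-needling interaction (12 or 10 per cell, with or without baseline adjustment, ρ = 0.5 assumed).
- State that, as allocated in section 2.4, A vs B is confounded with enrolment period, that end of treatment falls at week 3 for A and week 9 for B, and that the sham contrast only partly offsets these.

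The cost is wording. No visit, patient or measurement is added. The downside is that the frequency objective becomes openly exploratory, and the wording does not remove the allocation and timing limits.
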